**Association with structural brain changes.**
*Hypothesis 3:* Hyperexcitability is associated with a distinct pattern of cortical volumes and white matter alterations on structural MRI, particularly in hippocampal, medial temporal, and parietal regions.

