#### Structural MRI

2.3.2

All MRI examinations will be conducted on a 3T Siemens Magnetom Verio scanner using a 12-channel head coil. The protocol includes:

T1-weighted 3D MPRAGE (TR 2,300 ms; TE 3.4 ms; voxel 1 × 1 × 1 mm).Additional high-resolution T1-weighted 3D spoiled gradient echo (T1W 3D Turbo Field Echo; TR 9.7 ms; TE 4.6 ms; voxel 1 × 1 × 1 mm).T2-weighted, FLAIR, and 64-direction diffusion tensor imaging (DTI) sequences to evaluate lesions and white matter integrity.

Cortical reconstruction and volumetric segmentation will be performed using FreeSurfer 6.0 (“recon-all” pipeline with default parameters). Quality-checked outputs will provide cortical thickness and volume estimates in standard parcellations. DTI-based structural connectivity indices will be derived using established pipelines. The exact pipeline is described in previous studies published by our group (Bolla et al., 2025; Csukly et al., 2016).

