#### Cross-sectional analyses

2.6.1

Data from all diagnostic groups will be pooled into a single multivariate dataset and analyzed using machine learning and dimensional reduction techniques to extract cross-diagnostic patterns of neural and behavioral variance. The model will test for latent factors reflecting shared E/I imbalance across disorders, while *post hoc* analyses identify disorder-specific deviations. Statistical adjustments will account for confounders such as age, medication, and cognitive status.

Primary outcome will be the (Torenvliet et al., 2023) incidence and distribution of SEA, and fMRI hyperactivity in each diagnostic group relative to controls. Secondary outcomes will include relationships between hyperexcitability and (a) structural atrophy and white matter integrity; (b) functional connectivity within and between default mode, salience, and attention networks; (c) CSF and plasma tau/Aβ levels; and (d) domain-specific cognitive performance.

Incidence of hyperexcitability (primary outcome):○Logistic regression models comparing SEA and fMRI-positive status between groups (MCI, ASD, ADHD vs HC), adjusting for age, sex, education, and disease duration where applicable.○Results will be reported as odds ratios with 95% confidence intervals.

Associations with cognition, structure, and connectivity (secondary outcomes):○Within each group, participants will be classified as hyperexcitability-positive vs negative (see section “2.4.1 Participant selection and extraction of normative values”).○For continuous outcomes (neuropsychological scores, cortical thickness/volume, DTI measures, functional connectivity indices, blood-based biomarker concentrations), group comparisons will use *t*-tests or Mann–Whitney U tests depending on normality (Shapiro-Wilk).○For categorical variables, chi-square tests will be used.○Multivariable linear models with covariates (age, sex, education, disease duration, mood/anxiety scores) will assess independent associations.Holm–Bonferroni corrections will be used to control for multiple comparisons.

Cross-modal relationships:○Correlation and regression analyses will examine relationships between spike density and fMRI hyperactivity.○Multimodal latent variable models or clustering approaches will be applied exploratorily to define hyperexcitability phenotypes.

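### The volume analyses for Hypothesis 3 list no head-size adjustment, which costs precision and leaves any head-size difference between positives and negatives to be read as a volume effect

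*Protocol article*

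**What the plan says.** Hypothesis 3 (section 1.2) reads: "Hyperexcitability is associated with a distinct pattern of cortical volumes and white matter alterations on structural MRI", with hippocampal, medial temporal and parietal regions singled out. Section 2.6.1 makes the matching secondary outcome "relationships between hyperexcitability and (a) structural atrophy and white matter integrity".

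The measurements come from FreeSurfer 6.0 run with default parameters (section 2.3.2): "Quality-checked outputs will provide cortical thickness and volume estimates in standard parcellations". The same section adds: "The exact pipeline is described in previous studies published by our group".

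For the analysis, section 2.6.1 names cortical thickness and volume among the continuous secondary outcomes. Within each group, positives and negatives are compared by a t-test or a Mann–Whitney test, depending on a normality test. Then: "Multivariable linear models with covariates (age, sex, education, disease duration, mood/anxiety scores) will assess independent associations". Intracranial volume, head size or an equivalent term appears nowhere in the article.

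**The concern.** A regional brain volume reflects both the size of the head and any loss of tissue, and only the second is atrophy. A model meant to detect atrophy from volumes in a single scan therefore normally carries a head-size term. Sex stands in for head size only in part, and the two-group tests adjust for nothing.

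Two things are at stake for the volume part of Hypothesis 3. One is precision, because head-size variation left in the residual widens every interval, in comparisons where the positive group may be small. The other is interpretation, because a real head-size difference between positives and negatives could not be told apart from a volume effect. The second matters here because the Rationale (section 1.1) cites work in Alzheimer's disease that links subclinical epileptiform activity to larger overall cortical volumes. A global difference of that kind is also what a difference in head size would produce.

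**Working it through.** The plan gives no power or precision figure for the structural outcomes, so there is none to reproduce.

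**Inputs**
- Covariates: age, sex, education, disease duration, mood/anxiety scores (section 2.6.1).
- Group size: 75 (section 2.2.4).
- Share positive: about 15%. Section 2.2.4 gives this for planning the in-ward substudy; applying it within one diagnosis is an assumption. 0.15 × 75 = 11.25, so about 11 positive and 64 negative.
- Effect size d = 0.5, two-sided α = 0.05: given in section 2.2.4 for the primary outcomes, used here only for illustration.
- r, the correlation of a regional volume with intracranial volume after the listed covariates: not in the article. Assumed 0.3 to 0.6.

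**Step 1. Precision.** Adjustment removes a share r² of the residual variance. The equivalent sample-size factor is 1/(1 − r²).

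| r | Variance removed | Sample-size factor |
|---|---|---|
| 0.3 | 9% | 1.10 |
| 0.4 | 16% | 1.19 |
| 0.5 | 25% | 1.33 |
| 0.6 | 36% | 1.56 |

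**Step 2. Effect on power in one group.** The standard error of a difference, in SD units, is √(1/11 + 1/64) = 0.326. For d = 0.5 before adjustment, 0.5/0.326 = 1.53 and power is about 33%. With adjustment the effect in residual SDs becomes 0.5/√(1 − r²):
- r = 0.3: d = 0.524, power 36%
- r = 0.5: d = 0.577, power 42%
- r = 0.6: d = 0.625, power 48%

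**Step 3. No true head-size difference.** The omitted term is then unrelated to positive or negative status. Its variation is part of the standard error, and two-sided rejection under no volume effect stays at 5%.

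**Step 4. A true head-size difference.** If mean head size differs by δ SD, the apparent volume effect with no real one is r × δ. With b = rδ/0.326, the rejection rate is Φ(b − 1.96) + Φ(−b − 1.96). The values of δ are illustrations; the article gives none.
- δ = 0.2: apparent effect 0.06 SD (r = 0.3) or 0.10 SD (r = 0.5); rejection 5.4% or 6.1%
- δ = 0.5: apparent effect 0.15 SD (r = 0.3) or 0.25 SD (r = 0.5); rejection 7.5% or 11.9%

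**The case against.** The strongest reply is that the article never says the volumes are unnormalised. Section 2.3.2 hands the exact pipeline to earlier publications, and section 2.5 refers to harmonised procedures for MRI preprocessing. If volumes are scaled to head size when they are derived, the regression list rightly omits the term. This stands: it cannot be checked from the article, and the point has to be conditional on it. It does not remove the point, because section 2.6.1 itself sets out covariates for the volume models and a reader cannot tell from it that head size is handled.

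A related reply is that one sentence serves five families of outcome and may be a shared summary. The fMRI nuisance regressors, for example, sit in section 2.3.3 and not in this list. That is fair, but the fMRI terms are at least stated somewhere, and a head-size step is not.

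It is also true that volume is only part of the structural outcome. Thickness and diffusion measures are much less affected, section 3.2 discusses the result in terms of cortical thinning and white matter damage, and Hypothesis 3 predicts a distinct pattern, not simply smaller volumes. A reader might infer that small heads will be scored as atrophy and the test of Hypothesis 3 is biased. The documents do not support that: they give no evidence that head size differs between positives and negatives within a diagnosis.

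Nor does a chance imbalance between about 11 positives and 64 negatives show bias. That is ordinary sampling error, already in the standard error, and counting it separately would repeat the precision loss.

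**Conclusion.** The point holds as a conditional improvement to one component of a secondary outcome. As written, section 2.6.1 tests cortical volume without any head-size term, and the article states no normalisation. If none is done upstream, the volume models give away 9% to 36% of residual variance, equivalent to 10% to 56% more participants. This rests on the assumed residual correlation of 0.3 to 0.6. In a group split 11 to 64, that is a gain from about 33% power to between 36% and 48% at d = 0.5, so the comparison remains underpowered either way.

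Confounding is a possibility and has not been demonstrated. It arises only if head size truly differs between positives and negatives; otherwise type I error stays at 5%. The primary outcome is not touched.

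**What to change.** In section 2.6.1, add the estimated intracranial volume from the same FreeSurfer run as a covariate in the models for volume outcomes, and not in those for thickness. If volumes are already normalised to head size in the imaging pipeline, say so in section 2.3.2 or 2.6.1 instead. Make the head-size-adjusted model the test of the volume part of Hypothesis 3, and report the unadjusted t and Mann–Whitney results for volumes as descriptive.

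The cost is one degree of freedom in each volume model and a sentence in the plan. No new data are needed, and the article reports no results yet, so the choice can still be fixed in advance.

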#### Mechanistic analyses

2.6.2

Linear mixed-effects models will relate within-subject variation in SEA density to RAVLT performance, sleep spindle parameters, and plasma tau/Aβ levels, with random intercepts for participants.Connectivity changes (morning vs evening, SEA-rich vs SEA-poor epochs) will be assessed with paired tests and network-based statistics.Mediation models will explore whether sleep spindle disruption mediates the effect of SEA on overnight memory consolidation.

Effect sizes, confidence intervals, and model diagnostics will be reported systematically.

The entire analysis pipeline is highlighted in Figure 2.

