Patients with MCI, ASD, and ADHD frequently exhibit epileptiform discharges on electroencephalography (EEG) recordings, resting-state hyperactivity on functional magnetic resonance imaging (fMRI), and lower cortical excitability thresholds measured with transcranial magnetic stimulation (Takarae and Sweeney, 2017; Targa Dias Anastacio et al., 2022; Ugarte et al., 2023). In AD, subclinical epileptiform activity (SEA)—epileptiform discharges without overt clinical seizures—is increasingly recognized as a major contributor to accelerated cognitive decline (Kamondi et al., 2024; Vossel et al., 2026). Long-term EEG studies have demonstrated that SEA in AD is associated with faster cognitive deterioration and specific neuroanatomical substrates, including early precuneus thinning and larger general cortical volumes (Horvath et al., 2019; Nous et al., 2024). Previous observations have shown that sleep EEG is particularly sensitive to detect epileptiform activity in dementia (Horváth et al., 2017; Nous et al., 2024; Vossel et al., 2016). Some studies also suggest that SEA in dementia is associated with a special, probably more aggressive neuroimaging phenotype of AD (Cretin et al., 2016). Earlier reports have also demonstrated that SEA is linked to more rapid progression of cognitive decline in AD (Horvath et al., 2021; Vossel et al., 2013, 2016).

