#### In-ward protocol

2.4.2

Participants will be admitted to a dedicated video-EEG monitoring unit for three consecutive days and nights.

Continuous video-EEG: 34-channel scalp EEG (Micromed Morpheus, 10–20 system) will be recorded throughout admission, with peri-orbital leads for sleep staging.Memory paradigms: Three parallel versions of the RAVLT will be administered on consecutive evenings (7 pm).○Immediate recall (five learning trials) and delayed recall at 30 min.○Morning recall at ∼9 am to assess overnight retention.

Sleep analysis:○Visual staging of 20-s epochs according to AASM criteria (Moser et al., 2009).○Artifact annotation in 4-s segments.○Automated slow and fast spindle detection with Individual Adjustment Method (Bódizs et al., 2009).○Quantification of spindle density, duration, amplitude, and frequency over frontal (slow spindles) and centro-parietal (fast spindles) leads, in N2 and N3, and combined N2+N3.○Power spectral analysis of N2 and N3 for slow-wave sleep characteristics.Serial blood sampling: Evening and morning samples across the 3-day stay to estimate circadian patterns of plasma tau and Aβ.

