#### Data extraction and mechanistic analyses

2.4.3

For each participant, we will derive:

SEA density and temporal distribution across nights and days.Within-subject variability in RAVLT learning, 30-min retention, and overnight consolidation.Sleep architecture metrics and spindle parameters.Day–night and day-to-day changes in plasma tau/Aβ.

SEA density will be correlated with memory performance, spindle metrics, and biomarker levels, as assessed using mixed-effects models that account for repeated measures. Comparisons will be made between SEA-rich and SEA-poor epochs and between days with high vs low hyperexcitability burden. Group-specific patterns (e.g., MCI vs ASD vs ADHD) will be examined.

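### The in-ward model of plasma tau/Aβ on SEA density names no draw-time term, so a day-night pattern shared by both would bias the SEA slope

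*Protocol article*

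**What the plan says.** Section 2.6.2 (Mechanistic analyses) gives the model: "Linear mixed-effects models will relate within-subject variation in SEA density to RAVLT performance, sleep spindle parameters, and plasma tau/Aβ levels", "with random intercepts for participants". Section 2.4.3 describes the same analysis and adds only that relationships are "as assessed using mixed-effects models that account for repeated measures". Neither place names time of day or study day as a term in the plasma model.

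Section 2.4.2 (In-ward protocol) sets the sampling: "Evening and morning samples across the 3-day stay to estimate circadian patterns of plasma tau and Aβ". Section 2.4.3 lists among the quantities to be derived for each participant "SEA density and temporal distribution across nights and days" and "Day–night and day-to-day changes in plasma tau/Aβ".

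On the predictor, the Rationale (1.1) states: "Previous observations have shown that sleep EEG is particularly sensitive to detect epileptiform activity in dementia". Section 2.4.1 counts sleep state among the factors that influence EEG transients and adjusts the normative spike-density thresholds for it. Section 2.6.2 does name morning versus evening, but only as a contrast for connectivity.

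**The concern.** On the article's own account the outcome is expected to move with clock time, and the predictor may do so too. A random intercept removes stable differences between people. It does not remove a rhythm that everyone shares, and neither does centring SEA density on each person's mean. If SEA density is computed for the period before each draw, morning samples follow a night's sleep and evening samples follow a waking day. The within-person slope then mixes two things: whether more SEA than usual at a given clock time goes with a different protein level, and the plain fact that both series differ between morning and evening.

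At stake is the fourth knowledge gap in the Rationale, whether hyperexcitability modulates the burden or circadian dynamics of tau and amyloid. Section 3.1 also claims stronger inference about temporal relationships from these repeated measures. A shared rhythm could produce a positive answer with no SEA effect at all. Emphasis on estimation instead of testing does not help, because the estimate and its interval are displaced as well.

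**Working it through.** The article gives no power, effect size or error rate for this model, so there is no figure of its own to reproduce. The check asks how far the slope moves when the true SEA effect is zero.

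**Inputs from the article**
- Model: SEA density as within-subject predictor, participant random intercept (2.6.2).
- Draws: evening and morning over a three-day stay (2.4.2).
- Final in-ward sample: about 40 (2.2.4). I also ran 36, which is 45 × 0.8, the stated 20% attrition applied to the stated 45.
- Two-sided α = 0.05, stated in 2.2.4 for the primary study and assumed here.

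**Assumptions**
- Three evening and three morning draws per person. The article does not give the number.
- SEA density is matched to each draw. The article does not define the window.
- *a* is the day-night shift in SEA density and *c* the day-night shift in the protein, both in within-person SD. The article gives neither, so I use a range from 0 to 1.

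**Expected slope.** Code clock time as ±0.5. Over six draws its sum of squares is 6 × 0.25 = 1.5. Independent within-person variation contributes 6 − 1 = 5. Per person:
- within-person sum of squares of SEA: 1.5a² + 5
- within-person cross-product of SEA and protein: 1.5ac
- spurious slope: b = 1.5ac / (1.5a² + 5)

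**Standard error.** The residual variance is s² = [1.5c² + 5 − (1.5ac)² / (1.5a² + 5)] / 5, and SE = √{s² / [n(1.5a² + 5)]}.

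Example with a = c = 0.5 and n = 40:
- b = 0.375 / 5.375 = 0.070
- s² = (5.375 − 0.375² / 5.375) / 5 = 1.070
- SE = √(1.070 / 215) = 0.0705
- b / SE = 0.99, so a two-sided 5% test rejects about 17% of the time

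**Results, n = 40, true SEA effect zero (2,000 simulated datasets per setting)**

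| a (SEA) | c (plasma) | slope, formula | rejection, formula | rejection, simulated | simulated with morning/evening term |
|---|---|---|---|---|---|
| 0 | 0 to 1 | 0 | 5% | 4.3–5.6% | 5.2–5.6% |
| 0.25 | 0.25 | 0.018 | 5.8% | 6.0% | 5.0% |
| 0.5 | 0.5 | 0.070 | 16.7% | 16.7% | 5.1% |
| 0.5 | 1 | 0.140 | 44.0% | 42.9% | 5.0% |
| 1 | 1 | 0.231 | 91.8% | 92.6% | 4.8% |

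With 36 participants the last three simulated rates without the term are 16.3%, 41.4% and 89.6%. A full mixed-model fit at a = c = 0.5 and n = 40 (200 datasets) gave slope 0.066 and 18% rejection without the term, and −0.004 and 4.5% with it. Across all settings tried, rejection with the term was 4.2–5.6% at n = 40 and 4.3–5.8% at n = 36.

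**How much of the rhythm SEA absorbs.** The share of the protein's day-night change carried by the SEA term is ab/c = 1.5a² / (1.5a² + 5): 0% at a = 0, 7% at a = 0.5 and 23% at a = 1.

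**The case against.** The strongest reply is that this is a condensed article. Section 2.6.2 lists no fixed-effect covariates of any kind for the mixed models, not even age or diagnosis, and the full analysis plan may contain a draw-time term. That stands in part: the article does not exclude such a term, and a reader who infers that it was rejected goes further than the text. But the article does state predictor, outcomes and random structure, lists covariates for its cross-sectional models in 2.6.1, and names morning versus evening for connectivity only. Followed as written, the model can give a wrong slope.

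Second, the bias depends on how SEA density is defined. Section 2.4.3 also plans to compare days of high and low hyperexcitability burden. A per-day density is constant across that day's draws, so with a morning and an evening draw on each day a common day-night shift in the protein cannot load on it. This stands, and it is why the point is conditional.

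Third, a reader might infer that any ordinary day-night change in the proteins would be credited to SEA. The arithmetic does not support that: nothing is credited when SEA has no rhythm, and under a quarter at a shift of 1 SD. Nor does the article give a night-to-day SEA ratio. The Rationale speaks of sensitivity to detect epileptiform activity in dementia, while the substudy also takes controls and adults with ASD or ADHD.

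Fourth, one might extend the argument to the three word lists given on consecutive evenings, where practice, ward adaptation and list form could run with night order. The article does not say that list order is fixed, and bias would also need SEA to trend across nights. I have not quantified this and do not press it as a defect.

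Finally, 2.2.4 presents the substudy as estimating effect sizes and identifying candidate pathways, and 3.5 disclaims definitive causal inference. That lowers the stakes but does not correct a displaced estimate.

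**Conclusion.** The point holds in conditional form. The plasma model as stated names no term for draw time, although the sampling is built around two clock times and SEA is treated as sleep-linked. If SEA density is matched to each draw and both series shift between day and night, the slope is biased and the test anticonservative. The effect is negligible when both shifts are 0.25 SD, material from about 0.5 SD and severe at 1 SD. These sizes rest on assumed shifts, six draws per person, independent within-person errors and about 40 participants. If SEA has no day-night shift, or is used only as a per-day measure with draws balanced within each day, the problem does not arise. The remedy does not depend on which case applies.

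**What to change.** In 2.6.2:
- add fixed effects for draw time (morning versus evening) and study day to the SEA-plasma model, so that the SEA slope comes from differences at the same clock time;
- state the SEA window matched to each plasma draw;
- report the morning-evening plasma difference as a separate descriptive result.

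A night-number term in the overnight-recall model is a sensible minor addition.

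The cost is a few model terms and no new samples. The SEA slope becomes somewhat less precise, because the day-night contrast no longer feeds it. At a given residual SD, the draw-time term raises the standard error by a factor of about √[(1.5a² + 5) / 5], which is 1.04 at a = 0.5 and 1.14 at a = 1. Any residual variance that the term removes offsets part of this.

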#### Sample size justification

2.2.4

Power calculations for the primary cross-sectional study were informed by previous investigations of cortical hyperexcitability and subclinical epileptiform activity (SEA) in neurocognitive disorders [summarized by Horvath et al. (2020)]. Assuming a medium effect size (Cohen’s *d* = 0.5), a two-sided significance level of α = 0.05, and four diagnostic groups, a sample size of 75 participants per group (total *N* = 300) provides more than 90% power to detect clinically meaningful between-group differences in the primary outcomes, including the incidence of SEA and resting-state fMRI hyperactivity.

The mechanistic in-ward substudy is enrichment-based and will include participants demonstrating evidence of cortical hyperexcitability. Assuming a conservative prevalence of approximately 15% across the clinical groups, we anticipate recruiting approximately 45 eligible participants, with an expected final sample of approximately 40 after accounting for an estimated 20% attrition rate.

The mechanistic substudy is designed primarily to characterize within-subject physiological relationships among cortical hyperexcitability, sleep architecture, memory consolidation, and circulating biomarkers using repeated-measures analyses. Because repeated observations substantially increase statistical efficiency for within-subject comparisons, this sample size is considered appropriate for estimating effect sizes, assessing feasibility, and identifying candidate mechanistic pathways. In contrast, more analytically demanding models, including formal mediation analyses and subgroup comparisons across diagnostic categories, are expected to have limited statistical power with the anticipated sample size. Accordingly, these analyses will be considered exploratory and hypothesis-generating, with emphasis placed on effect size estimation, confidence intervals, and model uncertainty rather than statistical significance alone. Findings from these exploratory analyses will inform sample size calculations and analytic strategies for future confirmatory multicenter studies.

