
It should also be emphasized that the present study is not designed to establish that cortical hyperexcitability plays an identical mechanistic role across MCI, ASD, and ADHD. Instead, the multimodal framework is intended to identify both shared and disorder-specific characteristics of hyperexcitability. Subsequent analyses will therefore examine whether associations between SEA, functional network alterations, structural changes, sleep physiology, and cognitive performance differ between diagnostic groups. These comparisons will help determine whether cortical hyperexcitability represents a common downstream manifestation of distinct disease processes or reflects disorder-specific mechanisms with partially overlapping neurophysiological signatures.

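### The in-ward mixed models name a random intercept but no random SEA slope, so confidence intervals for the average SEA effect are too narrow if that effect differs between participants

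*Protocol article*

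**What the plan says.** Section 2.6.2 defines the target and the model in one sentence. "Linear mixed-effects models will relate within-subject variation in SEA density to RAVLT performance", and also to sleep spindle parameters and "plasma tau/Aβ levels, with random intercepts for participants". The same section says that effect sizes, confidence intervals and model diagnostics will be reported. Section 2.4.3 adds only that the mixed models take account of repeated measures.

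The substudy takes participants from all four groups, on SEA above a density threshold or on fMRI hyperactivity alone (section 2.4.1). Each person has three RAVLT evenings, and evening and morning blood samples over three days (section 2.4.2).

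Two places leave open that the SEA effect is not the same for everyone. Section 2.4.3: "Group-specific patterns (e.g., MCI vs ASD vs ADHD) will be examined". Section 3.2 says later analyses will "examine whether associations between SEA, functional network alterations, structural changes, sleep physiology, and cognitive performance differ between diagnostic groups".

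Section 2.2.4 starts from about 45 people, based on a prevalence near 15%, and ends "with an expected final sample of approximately 40 after accounting for an estimated 20% attrition rate".

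**The concern.** As written, the model is y_it = b0 + u_i + b1·SEA_it + e_it, with u_i the only random term. The random intercept deals with people having different outcome levels. It does not deal with people having different SEA slopes. Everyone is given the same b1, and each further night or blood sample counts as independent evidence on it. If slopes differ, observations from one person share that person's own departure from the average slope, and the model's standard error leaves out that component.

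Unequal SEA variability makes this worse. A participant admitted on fMRI alone may have little SEA to vary, while an SEA-rich participant has a lot. A few people can then carry most of the weight in the pooled slope.

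At stake are the intervals for SEA on memory, spindles and plasma tau/Aβ, which are the main output of the substudy. Centring SEA within person, or adding terms for night or clock time, does not remove the problem: the check below uses person-centred SEA and has no time effect.

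**Working it through.** **Inputs from the documents.** Repeats per person: T = 3 (RAVLT evenings) and T = 2 × 3 = 6 (plasma). Sample: 45 × (1 − 0.20) = 36. The plan's own figure of about 40 is not reproduced by this arithmetic, so 36 is used; 40 gives nearly the same error rates. The two-sided 5% level is stated for the cross-sectional study ("a two-sided significance level of α = 0.05") and is borrowed here as a yardstick. The plan states no error rate for the in-ward models.

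**Assumptions.** The true mean slope is 0, the residual SD is 1 and the within-person SD of SEA is 1. Person slopes are normal with SD τ = 0, 0.25 or 0.5. SEA spread is either equal across people or log-normal with log-SD 0.5. The documents give neither τ nor the spread.

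**Closed form, equal spread.** Let S_i be person i's sum of squares of centred SEA. The common slope is Σ S_i b_i / Σ S_i. With normal SEA, E(S_i) = T − 1 and E(S_i²) = (T − 1)(T + 1), so approximately:

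- true variance = [1 + τ²(T + 1)] / [(T − 1)N]
- variance the model reports = (1 + τ²) / [(T − 1)N]
- ratio R = [1 + τ²(T + 1)] / (1 + τ²)
- false-positive rate ≈ 2[1 − Φ(1.96/√R)]

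| T | τ | R | √R | Rate |
|---|---|---|---|---|
| 3 | 0.25 | 1.25/1.0625 = 1.18 | 1.08 | 7.1% |
| 3 | 0.5 | 2/1.25 = 1.60 | 1.26 | 12.1% |
| 6 | 0.25 | 1.4375/1.0625 = 1.35 | 1.16 | 9.2% |
| 6 | 0.5 | 2.75/1.25 = 2.20 | 1.48 | 18.6% |

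At τ = 0, R = 1 and the rate is 5%.

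**Simulation, N = 36, 10,000 runs per cell.** For balanced, person-centred SEA, the random-intercept test equals the common-slope test.

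| Setting | τ = 0 | τ = 0.25 | τ = 0.5 |
|---|---|---|---|
| 3 nights, equal spread | 4.9% | 6.9% | 12.1% |
| 3 nights, unequal spread | 5.1% | 9.8% | 19.6% |
| 6 samples, equal spread | 4.9% | 8.9% | 17.7% |
| 6 samples, unequal spread | 5.1% | 14.6% | 30.4% |

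The equal-spread rows agree with the closed form. Separate batches differ by about a percentage point, which gives the rounded ranges quoted in the conclusion.

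**Interval width, equal spread.** At τ = 0.5 and T = 3, the model reports √(1.25/72) = 0.132 against a true √(2/72) = 0.167, so the interval is about 21% too narrow. At T = 6 it reports √(1.25/180) = 0.083 against √(2.75/180) = 0.124, about 33% too narrow. At τ = 0.25 the shortfalls are 1 − 1/1.08 ≈ 8% and 1 − 1/1.16 ≈ 14%.

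**Alternatives.** A random-slope REML fit with t on N − 1 degrees of freedom (N = 40) gives about 4-7% in every setting tried. CR2 standard errors with Satterthwaite degrees of freedom (N = 36) give about 4-6.5%. Plain CR1 clustered standard errors are not enough: under unequal spread they reach about 6-12%.

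**The case against.** **The inflation is assumed, not documented.** This stands. The documents give no slope SD. At 0.25 with equal spread and three nights the rate is only about 7%. A reader might infer that inflation of 12% to 30% is a property of the plan. It is not: those values need a slope SD of 0.5, and the top end also needs unequal SEA spread.

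**The protocol does not predict varying slopes.** Also correct. Sections 2.4.3 and 3.2 say that differences by diagnosis will be examined, not that they are expected, and they speak of diagnostic groups rather than individuals. They do show that one common slope is not a premise of the protocol.

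**Repeats do help.** A reader might infer that the argument in section 2.2.4, "Because repeated observations substantially increase statistical efficiency for within-subject comparisons, this sample size is considered appropriate", fails. It does not. At τ = 0.5 the true standard error falls from 0.167 to 0.124 between three and six repeats, about 26%.

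**The substudy estimates rather than tests.** Section 2.2.4 speaks of effect sizes, feasibility and candidate pathways, and no significance rule is set for the in-ward models. A reader might infer that null effects will be declared too often; the documents do not support that. The false-positive rate serves here as a measure of interval coverage. The exploratory label, with its emphasis on intervals and model uncertainty, is attached to the mediation and subgroup analyses, not to these models. The intervals for these models are promised in section 2.6.2.

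**The rest may be in an analysis plan.** Degrees of freedom and convergence rules could well be there. But the article does not leave the random-effects structure open: it names one, and nothing elsewhere in it adds to that. The promise of model diagnostics does not say what would follow from finding slope variation.

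**Three nights barely identify a random slope.** Fair, and the reason a fallback has to be named.

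**Conclusion.** The point holds as a conditional weakness in a stated analysis choice. For a within-person slope in a mixed sample, a random intercept alone gives standard errors and confidence intervals that are too small whenever slopes differ between people.

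With about 36 participants and a nominal 5%, the error rate is:

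- 5% with no slope variation
- about 6-10% (three nights) or 8-15% (six plasma samples) at a slope SD of 0.25 residual SD per within-person SD of SEA
- about 12-21% or 18-32% at a slope SD of 0.5

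The upper ends require SEA variability that is unequal across people. Both slope SDs and the unequal spread are assumptions. The effect is larger for the plasma models than for the memory models. It does not undermine the sample-size rationale, but it should be corrected because the remedy is cheap.

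**What to change.** In section 2.6.2, replace the random-effects clause with: *random intercepts and random SEA slopes for each participant, with small-sample degrees of freedom; where the random slope cannot be estimated (likely with three nights), a random intercept with participant-clustered CR2 standard errors and Satterthwaite degrees of freedom.*

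Section 2.2.4 needs no change on this account.

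The cost is one sentence and no new data. If slopes do not in fact vary, intervals widen slightly: with 40 participants the simulated standard error goes from 0.113 to 0.118 with three nights and from 0.071 to 0.074 with six samples, about 4% in each case. There is a correspondingly small loss of power.
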